***Primary outcome measure***						
TTP		✓			✓	
***Secondary outcome measures***						
Symptoms (Neuro-check)		✓	✓		✓	✓
Blood pressure		✓	✓		✓	✓
ECG		✓	✓		✓	
DEC		✓			✓	
Blood/plasma viscosity		✓		✓		✓
Blood coagulation profile		✓		✓	✓	✓
CCr		✓		✓	✓	
Lipid profile		✓			✓	✓
MMSE		✓			✓	✓
**Patients With Stroke**	NIHSS	✓			✓	✓
	BI	✓			✓	✓
	mRS	✓			✓	✓

*ECG*, Electrocardiogram; *DEC*, Doppler Echocardiography; *CCr*, Creatinine clearance; *MMSE*, Mini-mental State Examination; *NIHSS*, National Institutes of health Stroke Scale, *BI*, Barthel Index; *mRS*, modified Rakin Scale.

### Study procedures

Figure 1 shows the trial procedure. Participants with suspected unilateral ICA or MCA stenosis will firstly receive CT and CTP brain scanning to exclude the intracranial hemorrhage and be confirmed their cerebral perfusion state. Patients with unilateral cerebral hypoperfusion will be further evaluated by physicians in participating hospitals according to a series of evaluation procedure, including history taking, complete physical examination, radiology tests and relative laboratory tests (Table 1). For radiology tests, MRI brain scanning will be applied to confirm whether a consistent infarct exist in hypoperfusion region or not, and DSA will be performed to determine the degree of artery stenosis/occlusion. Once a standardized, structured interview is performed, the data will be recorded in the case report form for each patient. All clinical data, biological samples and radiological images would be sent to the central study site where a cerebrovascular neurologist would review the data. For the patients with non-acute ischemic stroke, National Institutes of Health Stroke Scale, Barthel Index and modified Rakin Scale will be performed by an individual researcher. Demographic, medical, social, and behavioral variables will be determined along with baseline medications. Anthropometry will be conducted using standardized equipment calibrated on a daily basis.

**Figure 1 F1:**
[figure not shown]
Flowchart outlining the trial protocol.

Participants will be randomized to one of two interventions: HES 130/0.4 and NS with two daily dosages in each intervention, i.e. 500 ml and 1000 ml, for 7 consecutive intervention days. A range of outcome measures (Table 1) will be used to ensure evaluation of relevant variables, based on the primary and secondary aims of the trial, clinical relevance and feasibility. Patients will be enrolled initially in the 500 ml groups. If more than 30% patients experience intolerable adverse events, the trial should be stopped. Following successful completion of 500 ml dose study, patients should be enrolled in the 1000 ml groups.

According to our preliminary study, 60% (15/25) of patients were found infarct responsible focuses in MCA territory by MRI brain scanning. To ensure comparable groups in terms of neurological status, group assignment will be stratified by having infarct responsible focuses or not. An individual not associated with the trial will use a computerized random number generator to randomly assign subjects to group. Allocation concealment will be ensured by using opaque, a sealed envelope containing group assignment.

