### Study design

Multicenter, randomized, paralleled, double-blinded trial with concealed allocation of patients with cerebral hypoperfusion 1:1 to volume therapy using 6% HES 130/0.4 in 0.9% sodium chloride (Voluven, Fresenius Kabi, Germany) or 0.9% sodium chloride solution (normal saline, NS), is stratified by presence of stroke or not. We use digital subtraction angiography (DSA) to verify the severity of ICA or MCA stenosis [21], and evaluate cerebral hypoperfusion in unilateral intracranial artery territories by time to peak (TTP), one of parameters in CTP imaging [22].

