### Sample size estimates

The results from our preliminary study were used to calculate the sample size (unpublished data). The mean difference and standard deviation of TTP after HES 130/0.4 were 19.83 and 10.21, respectively. A two-sided 5% significance level and 80% power were considered, and the following equation was used: 

$$n=\frac{2\times {\left(\zeta_{\alpha /2}+\zeta_{\beta }\right)}^{2}\times \sigma^{2}}{\delta^{2}}$$

Approximately 60 participants in each group were calculated to be required. A 20% attrition rate is anticipated over the 2-year study period, resulting in about 300 participants in total four groups as a final estimated sample size.

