### Randomization procedures

Random number will be generated by a computerized random-number generator at statistics research office, Fourth Military Medical University. A clinical research associate will make opaque blinded envelopes (with consecutive numbers) and deliver them to each participating center. Random allocation will be performed within 12 hour after a patient enrolled. The block size and treatment-assignment table will not be available to the researchers until the end of the trial.

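### The 30% stopping rule before the dose doubles names no arm, so blinded researchers can apply it only to HES and saline pooled; tie it to the HES arm

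*Protocol article*

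**What the plan says.** All of this is in the protocol article.

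- **Study procedures (text after Figure 1).** The doses are sequential: "Patients will be enrolled initially in the 500 ml groups". The groups are plural because each dose has an HES arm and a saline arm. The safety limit follows: "If more than 30% patients experience intolerable adverse events, the trial should be stopped". Then comes escalation: "Following successful completion of 500 ml dose study, patients should be enrolled in the 1000 ml groups". No arm, denominator or look time is attached to the 30%.
- **Study design.** "Multicenter, randomized, paralleled, double-blinded trial with concealed allocation of patients with cerebral hypoperfusion 1:1 to volume therapy".
- **Randomization procedures.** "The block size and treatment-assignment table will not be available to the researchers until the end of the trial". The list itself is produced outside the clinical team: "Random number will be generated by a computerized random-number generator at statistics research office".
- **Sample size estimates.** About 60 per group before 20% attrition, "resulting in about 300 participants in total four groups as a final estimated sample size".
- **Intervention.** Saline patients receive the same daily volume as HES patients. The cumulative doses are 3500 ml and 7000 ml. The risks named for overdose are circulatory overload and brain edema.
- **Other safety oversight.** Table 1 lists daily checks of symptoms, blood pressure and ECG. Study procedures adds: "All clinical data, biological samples and radiological images would be sent to the central study site where a cerebrovascular neurologist would review the data". Neither carries a numerical threshold.

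**The concern.** The limit is meant to show whether 500 ml of HES a day is tolerated well enough to try 1000 ml. It is set on patients in general, and half of the patients in that stage receive saline. Researchers who cannot see the assignments have only one way to apply it: all intolerable events divided by all patients. Saline patients then dilute any problem specific to HES.

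This is the only numerical gate stated before the daily dose doubles. The higher cumulative dose, 7000 ml, lies above the top of the range that the Intervention section cites from resuscitation use (328 to 6229 ml). If intolerable events come mainly from HES itself, the pooled count can open the 1000 ml stage while the HES rate is above the sponsor's own 30% limit.

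**Working it through.** **Group size.** 60 / (1 − 0.20) = 75 per group, and 4 × 75 = 300, which reproduces the stated total. The 500 ml stage is therefore 75 HES and 75 saline. I take the 60 as given.

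**Break-even.** With 1:1 allocation the expected pooled rate is (HES rate + saline rate) / 2. This exceeds 30% only if the HES rate exceeds 60% − saline rate: 55%, 50% and 40% for saline at 5%, 10% and 20%.

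**Event rates.** The document gives none. All rates below are assumptions, shown over a range.

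**One look at the end of the stage (exact binomial).** More than 30% means at least 46 of 150 pooled, or at least 23 of 75 in the HES arm. The pooled probability is P(X + Y ≥ 46) with X ~ Bin(75, HES rate) and Y ~ Bin(75, saline rate). The HES-arm probability is P(X ≥ 23).

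| True HES rate | Saline 5% | 10% | 20% | 25% | 30% | 40% | HES-arm count |
|---|---|---|---|---|---|---|---|
| 40%, pooled | 0.7% | 6% | 46% | 71% | 89% | 99% | 96% |
| 35%, pooled | 0.05% | 0.9% | 21% | 46% | 71% | – | 82% |

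With 60 per arm (cut-offs 37 of 120 and 19 of 60), HES at 40% and saline at 5% or 10% give 1% or 7% pooled, against 93% in the HES arm. The result does not depend on the exact group size.

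**Running count.** The rule states no look time, so it may be meant to run throughout the stage. I simulated a count applied continuously from 20 patients on (the start point is an assumption), with 75 per arm. At HES 40% and saline 5%, 10% or 20%, the pooled count stops with probability about 30 to 33%, 49 to 52% or 84 to 85%, depending on how the looks are coded. The HES-arm count stops with probability about 99%. At HES 35% and saline 20% the pooled figure is 71%, compared with 21% at a single look. The gap is narrower than with one look but remains large when the saline rate is low.

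**Chance stops.** With a single look, the HES-arm count stops with probability 2% at a true HES rate of 20% and 16% at 25%. The pooled count with both arms at 25% stops with probability 7%. Adding one look halfway (75 patients) raises the HES-arm figures to about 6% and 27%, and the pooled 25%/25% figure to about 18%.

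**The case against.** **A condensed article may leave this to the full protocol.** An unblinded monitor may be named there. That stands as a caveat. But the article itself states the threshold, the escalation step, the blinding and the closed table, and the stated rule does not ask for a count by arm.

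**A reader might infer that the trial cannot count by arm, or that the protocol prescribes a pooled count.** Neither is supported. The table is closed to the researchers only. The statistics office, and the unassociated individual who assigns patients, stand outside the clinical team and could count by arm. The pooled reading is what follows for the blinded researchers.

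**A reader might also infer that the rule would almost never stop the trial.** The figures of 0.7% and 6% depend on a single look at the end. The wording fits a running rule equally well, and then the pooled count stops far more often.

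**The harmful case is not shown to be likely.** It needs intolerable events at 35 to 40% on HES with saline at or below about 20%, at the lower dose. The overdose risks the article names are volume risks, and saline patients get the same volume. If both arms share the rate, pooling does no harm; with both at 40% it stops slightly more often (99% against 96%). On the other side, HES allergy is an exclusion, and kidney function and coagulation are tracked outcomes, so effects specific to HES are not ruled out in advance.

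**Escalation also requires successful completion of the 500 ml stage.** It does, but the article attaches no other numerical criterion to success.

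**Conclusion.** The point holds as a weakness in a stated rule, with a cheap remedy. As written, blinded researchers can apply the 30% limit only to HES and saline together, and it then protects against an HES-specific problem only when the HES rate exceeds 60% minus the saline rate.

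The size depends on two things the document does not give: the event rates by arm and the look schedule. At HES 40% and saline 5 to 20%, pooling lowers the probability of stopping from 96% to between 0.7% and 46% with one look, or from about 99% to between about 30% and 84% with a running count. At saline 30% the single-look gap is small (89% against 96%), and it disappears when both arms share the rate. The document does not show that HES would cause such rates or that the 1000 ml stage would be unsafe. Confidence is medium.

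**What to change.** State in an amendment that:

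- the 30% limit applies to the HES 500 ml arm;
- the count is tabulated by the statistics office, outside the blinded team, with the saline count beside it so that background events can be judged;
- only continue or stop is reported to the investigators;
- the limit is formally checked before the 1000 ml groups open, and the trial can still be stopped earlier during the 500 ml stage. A single check at the end must not replace that, because it would leave all of roughly 150 patients to be treated before the limit could act.

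**Cost.** One or two sentences and a tabulation, with no extra patients. One person outside the blinded team sees safety data by arm. The smaller denominator gives more chance stops: with a single look, 16% at a true HES rate of 25%, against 7% pooled with both arms at 25%, and more with repeated looks. The number of formal looks should therefore be stated.

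Stopping only at 25 or more of 75 would bring the 16% back to 7%. It would also lower stopping from 82% to 66% at HES 35% and from 96% to 90% at HES 40%, and it moves the limit to 33%. The threshold and the definition of an intolerable event remain the sponsor's decision.

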### Intervention

All participants will receive routine medications including antiplatelet therapy, statins therapy, risk factor modification and others if necessary. Intervention group will receive a prescribed dose of 0.6% HES 130/0.4 in 7 intervention days. Control group will be treated the same volume of NS each day in the intervention period. The initial 10–20 ml will be infused slowly, keeping the patient under close observation.

Although, the infusion dose of HES 130/0.4 up to 33 mL/kg/day is most commonly used in clinical trials and repetitive large doses of up to 70 ml/kg/day have been reported in the literatures [23-26]. Considering potential risks of overloading the circulatory system and increasing brain edema by overdose and the median cumulative HES dose (2465 ml, range 328 ml to 6229 ml) in resuscitation [27], two dose groups (500 ml/day and 1000 ml/day) have been chosen as cumulative dose of 3500 ml and 7000 ml.

### Statistical analysis

Data will be exported into SPSS V15.0 software for subsequent analyses. A statistical analysis plan will be drafted at the start of the project and all analyses will be carried out after masking allocation. Independent samples t-tests, Mann–Whitney U tests and Chi-square test of association will be used as appropriate to compare groups at baseline. ANOVA or logistic regression will be used to determine significance of the results obtained.

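### The efficacy methods named are ANOVA or logistic regression, without baseline TTP as a covariate or the stroke/infarct stratum as a factor, and baseline differences are to be significance-tested; ANCOVA would be a free improvement

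*Protocol article*

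**What the plan says.** Under Statistical analysis, the efficacy method is given in one sentence: "ANOVA or logistic regression will be used to determine significance of the results obtained". No covariate or factor is named. The sentence before it reads "Independent samples t-tests, Mann–Whitney U tests and Chi-square test of association will be used as appropriate to compare groups at baseline". The same section announces a separate statistical analysis plan, which is not shown.

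Two variables that could enter the model are already available:

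- **Baseline TTP.** Table 1 schedules TTP at baseline and post-intervention, and prolonged TTP is an inclusion criterion. Under Primary outcome measure, the endpoint is the alteration of TTP at 7 days, described as improvement of hypoperfusion, without a formula or cut-off.
- **The randomisation stratum.** Study design stratifies by presence of stroke. Study procedures says that "group assignment will be stratified by having infarct responsible focuses or not", with the aim of making groups comparable in neurological status.

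Sample size estimates uses a two-means formula: "A two-sided 5% significance level and 80% power were considered", "The mean difference and standard deviation of TTP after HES 130/0.4 were 19.83 and 10.21, respectively" and "Approximately 60 participants in each group were calculated to be required".

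**The concern.** When an outcome is measured before and after treatment, the baseline value usually predicts the later one. ANCOVA removes that predictable part from the error term, and in large samples it is at least as precise as comparing change scores or post-treatment values alone. A factor used to stratify randomisation should normally also be in the model. Stratification balances the factor between groups, but an analysis that omits it still counts its variance as error, so the standard error is somewhat too large and the test slightly conservative.

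The baseline tests are a separate, smaller matter. With concealed random allocation, any baseline difference is due to chance. A p-value for it answers no useful question and does not identify which variables deserve adjustment.

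What is at stake is precision and clarity of the primary comparison, not bias.

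**Working it through.** **1. Inputs.** From Sample size estimates: two-sided 5%, 80% power, mean difference 19.83, SD 10.21, about 60 per group, 20% attrition, about 300 in four groups. The correlation r between baseline and day-7 TTP and the share of variance explained by the stratum (R²) are not given. Ranges are assumed for both.

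**2. The plan's own figure.** The printed formula is n = 2(z_α/2 + z_β)²σ²/δ², with (1.960 + 0.842)² ≈ 7.849.

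- As printed (δ = 19.83, σ = 10.21): n = 2 × 7.849 × 10.21²/19.83² = 4.16, so 5 per group. This does not reproduce 60.
- Exchanged (δ = 10.21, σ = 19.83): n = 2 × 7.849 × 19.83²/10.21² = 59.2, so 60 per group. Then 4 × 60 = 240, and 240/0.80 = 300. Both stated figures are reproduced.

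The exchanged order is therefore an inference, and the power figures below depend on it.

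**3. Unadjusted power at 60 per group.** Power = Φ(δ/(σ√(2/n)) − 1.96).

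- Exchanged: 10.21/(19.83 × √(2/60)) = 2.82, and Φ(0.86) = 80.5%.
- As printed: about 100%, so adjustment could add nothing visible.

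**4. Variance factor from ANCOVA.** Assume equal variance s² at both times. The residual variance after ANCOVA is s²(1−r²). A day-7-only analysis has variance s², so the ratio is 1−r². A change score has variance 2s²(1−r), so the ratio is (1+r)/2.

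**5. Power with ANCOVA**, one dose comparison, 60 per group, exchanged inputs:

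| r (assumed) | 1−r² | Power if 19.83 is the SD of day-7 TTP | (1+r)/2 | Power if 19.83 is the SD of the change |
|---|---|---|---|---|
| 0.3 | 0.91 | 84.0% | 0.65 | 93.8% |
| 0.5 | 0.75 | 90.3% | 0.75 | 90.3% |
| 0.7 | 0.51 | 97.7% | 0.85 | 86.4% |

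On the change-score reading the gain shrinks as r rises: at r = 0.9 power is 82.5%, against 80.5% unadjusted.

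**6. The stratum alone** (same inputs; residual SD = σ√(1−R²)). If the stratum is left out of the test, the true two-sided alpha is 2[1 − Φ(1.96/√(1−R²))].

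| R² (assumed) | Power with the stratum in the model | True alpha if it is omitted |
|---|---|---|
| 2% | 81.3% | 4.8% |
| 5% | 82.5% | 4.4% |
| 10% | 84.4% | 3.9% |

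**7. If dose cohorts are pooled.** Four groups of 60 give 120 per arm. On the exchanged inputs unadjusted power is then already about 98%, so the gain in step 5 applies only to a single dose comparison.

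**The case against.** The strongest reply is that the criticism rests on what one condensed sentence leaves out. ANOVA can carry the stratum and dose as factors, logistic regression can carry covariates, and covariate lists commonly sit in the analysis plan that the article announces. That stands: the text does not say the models will be unadjusted, and the missing list is no fault in itself. What remains is that ANCOVA on variables already collected is a better choice than the method named.

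Three stronger readings are tempting, and the document supports none of them.

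- **That the plan ignores baseline TTP.** The endpoint is an alteration of TTP, which reads as a change from baseline and so would use it. The fair statement is that baseline TTP is not named as a covariate.
- **That the primary outcome may be dichotomised, or the method picked after seeing results.** The sentence covers all results, and the secondary outcomes include vascular events and impaired organ function. ANOVA for continuous outcomes and logistic regression for binary ones is the ordinary reading, and the sample size is built on a mean difference. No cut-off or split of TTP is proposed anywhere.
- **That a known amount of power is wasted.** Neither r nor the stratum's R² is given, and on the printed inputs nothing is lost.

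It is also fair to say that no model choice is tied to the baseline tests, so they do not affect the primary inference.

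**Conclusion.** The point holds as a free improvement. The named efficacy methods include neither baseline TTP as a covariate nor the randomisation stratum as a factor, and the planned baseline tests are uninformative after randomisation.

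The direction of the gain is secure: with equal variances, (1+r)/2 is below 1 for any r below 1, and 1−r² is below 1 for any non-zero r. Its size is conditional. The rise from about 80% to about 84–98% needs r between 0.3 and 0.7, a single dose comparison with 60 analysed per group, and effect and SD in the order that reproduces 60. Omitting the stratum would err on the conservative side, by an amount that depends on an R² the document does not give. None of this implies a biased treatment estimate.

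**What to change.** Reword Statistical analysis, or settle it in the announced analysis plan before unblinding:

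- Primary analysis: ANCOVA of continuous post-intervention TTP on treatment, with baseline TTP on the same scale and the infarct/stroke stratum as used in randomisation. Add dose cohort if the cohorts are pooled.
- Logistic regression only for outcomes that are truly binary.
- Baseline characteristics described by group, without significance tests.

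The cost is wording only. Every variable is already collected, and no visit, measurement or patient is added. The effect and SD in Sample size estimates should be checked at the same time, because any statement about power depends on their order.

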## Discussion

Because of the lack of reliable clinical data, the effect of volume therapy (HES 130/0.4) on cerebral hypoperfusion due to severe ICA/MCA stenosis or occlusion is largely unsettled. In this trial, three types of patients with cerebral hypoperfusion will be recruited: non-acute ischemic stroke, TIA and asymptomatic patients. Although volume therapy could possibly decrease blood viscosity and may increase cerebral perfusion or oxygen delivery, previous studies [13,24,28] focused on acute ischemic stroke with treatment windows from 6 hours to 48 hours resulted no improvement in outcome or survival at the endpoints. In this trial, we’d like to enroll patients with non-acute ischemic stroke (time of stroke onset: 72 hours to 3 weeks) for the following reasons: 1. variable cerebral hypoperfusion state and higher risk of hemorrhagic transformation may appear in patients with acute ischemic stroke (< 72hours); 2. from 72 hours to 3 weeks of stroke onset, patients’ emotional state and cerebral auto-regulation are relatively stable. Cerebral hypoperfusion with severe intracranial atherosclerosis is one of common causes of ischemic stroke and TIA. Unless the collateral blood supply is sufficient to prevent ischemia, multiple remote spot-like infarctions may occur within the hypoperfused brain territory. Certainly, the superiority of surgical interventions over medical therapy has been confirmed in symptomatic patients with severe ICA stenosis [8,29]. However, for the asymptomatic patients with severe or moderate ICA stenosis, the role of surgical interventions remains uncertain. For the patients with ICA or MCA occlusion, medication could be the only practical therapy. Unfortunately, few effective medical treatments have been developed for the treatment of cerebral hypoperfusion. In this trial, we will use NS as control to compare the effect of HES 130/0.4 on the improvement of cerebral hypoprefusion in MCA territory. By using CTP imaging to confirm the brain perfusion state [30], this trial will contribute to study the effectiveness, safety and tolerability of safety of HES 130/0.4 for patients with chronic cerebral hypoperfusion.
